## Abstract

**Background:**

A considerable proportion of contemporary youth have a high risk of obesity-related disorders such as cardiovascular disease, metabolic syndrome, or non-alcoholic fatty liver disease (NAFLD). Although there is consistent evidence for the positive effects of physical activity on several health aspects, most adolescents in Colombia are sedentary. It is, therefore, important to implement strategies that generate changes in lifestyle. The HEPAFIT study aims to examine whether a 6-month exercise program has benefits for hepatic fat content and cardiovascular health outcomes among overweight/obese adolescents from Bogotá, Colombia.

**Methods/design:**

Altogether, 100 hundred overweight/obese, sedentary adolescents (aged 11–17 years) attending two public schools in Bogotá, Colombia, will be included in a parallel-group randomized controlled trial. Adolescents will be randomly assigned to an intervention group following one of four curricula: (1) the standard physical education curriculum (60 min per week of physical activity, *n* = 25) at low-to-moderate intensity; (2) a high-intensity physical education curriculum (HIPE, *n* = 25), consisting of endurance and resistance games and non-competitive activities, such as running, gymkhanas, lifting, pushing, wrestling, or hauling, for 60-min sessions, three times per week, with an energy expenditure goal of 300 to 500 kcal/session at 75–85% maximum heart rate (HRmax); (3) a low-to-moderate intensity physical education curriculum (LIPE, *n* = 25) consisting of endurance and resistance games and non-competitive activities (e.g., chasing, sprinting, dribbling, or hopping) for 60-min sessions, three times per week with an energy expenditure goal of 300 kcal/session at 55–75% HRmax; and (4) a combined HIPE and LIPE curriculum (*n* = 25). The HIPE, LIPE, and combined interventions were performed in addition to the standard physical education curriculum. The primary outcome for effectiveness is liver fat content, as measured by the controlled attenuation parameter 1 week after the end of the intervention program.

**Discussion:**

The translational focus may be suitable for collecting new information in a school setting on the possible effects of physical activity interventions to reduce liver fat content and to improve metabolic profiles and the cardiometabolic health of overweight/obese adolescents. This may lead to the more efficient use of school physical education resources.

**Trial registration:**

ClinicalTrials.gov, NCT02753231. Registered on 21 April 2016.

**Electronic supplementary material:**

The online version of this article (10.1186/s13063-018-2721-5) contains supplementary material, which is available to authorized users.

## Background

Pediatric non-alcoholic fatty liver disease (NAFLD) is considered the hepatic manifestation of metabolic syndrome and is the most common early driver of chronic liver disease in the United States [1]. However, the true prevalence of pediatric NAFLD is still not known for the following reasons: (i) to date, only a few population studies have been conducted in pediatric populations, (ii) different screening or diagnostic methods were used, and (iii) sex and ethnic differences were also reported [2]. In obese child populations, the prevalence of NAFLD ranges between 7.6% and 34.2% [3]. Moreover, the prevalence of NAFLD has increased in parallel with the prevalence of obesity, metabolic syndrome, and type 2 diabetes [2]. There is an association between obesity, especially abdominal obesity, with visceral adipose tissue and hepatic fat. Obesity induces metabolic disorders, such as NAFLD, through diverse pathways that involve adipocytokines, insulin and leptin resistance, overproduction of free radicals, and inflammation of adipose and liver tissue. If body fat is accumulated predominately in the upper body or abdominal cavity, the fat is mainly visceral, which has a greater impact on liver fat content and also positively correlates with the potential for developing NAFLD [4, 5].

The metabolic complexity of NAFLD presents challenges for a deeper understanding of the metabolic pathways that contribute to the development of this pathology [6, 7]. In the last few years, a growing number of studies have demonstrated that non-traditional biomarkers (Additional file 1: Table S1) that function as regulators of metabolic function may be involved in the etiopathogenesis of NAFLD and other metabolic disorders [8, 9]. Progress may be aided by a comprehensive metabolic analysis of the condition before and after the disease is established. Thus, several studies have observed that oxidative stress, inflammation, and insulin resistance are implicated in several aspects of glucose homeostasis and lipid metabolism and are associated with the pathogenesis and progress of NAFLD [10]. Moreover, non-traditional biomarkers may be used to assess biological adaptations to physiological changes or environmental exposures, such as lifestyle intervention programs based on increasing physical activity levels, improving dietary habits, and promoting a healthy weight. Likewise, the measurement of non-traditional and classical biomarkers, such as hepatic metabolism and cardiovascular biomarkers, presents an opportunity to evaluate biological changes associated with lifestyle interventions to reduce metabolic disorders associated with NAFLD progression, such as oxidative stress, inflammation, and insulin resistance.

There is evidence that sedentary lifestyles and unhealthy diets (especially those that are high in fats, free sugars, and salt) are driving the obesity epidemic and its co-morbidities in pediatric populations [11]. However, no medications or surgical procedures have been approved for the treatment of NAFLD. In turn, regular physical exercise has been shown to promote positive adaptations among obese children and adolescents [12]. Currently, there are no dietetic or physical activity guidelines for the management of NAFLD in children and youth. However, practice guidelines from the American Association for the Study of Liver Diseases have recommended lifestyle interventions to reduce body weight by 7–10% as the primary prevention and management of NAFLD in adults [13]. A recent meta-analysis in an obese pediatric population supports the current recommendation for physical exercise, mainly aerobic, as an effective intervention to counteract NAFLD progression by targeting hepatic lipid composition, visceral adipose tissue, and subcutaneous adipose tissue [14]. Still, the optimal exercise type (aerobic, resistance, or combined exercise training) and intensity (moderate or vigorous) to slow NAFLD progression in young populations is unclear.

Previous systematic reviews and meta-analyses in obese children and adolescents have shown that exercise reduces cardiometabolic risk factors, such as visceral adiposity [14], insulin resistance [12], inflammatory biomarkers [15], and hepatic lipid composition [14]. In addition, a growing body of evidence has demonstrated comparable or superior improvements in cardiometabolic health outcomes using low-volume, high-intensity interval training (HIIT) compared with traditional moderate-intensity continuous training (MICT) in adults [16] and the young population [17]. In a clinical setting, HIIT is an effective way of performing high-intensity exercise training and developing a high level of cardiorespiratory fitness [16]. A recent meta-analysis of 28 trials confirmed that both MICT and HIIT elicit large improvements in peak VO_2_ of healthy, young to middle-aged adults, with the effects being greater for the less fit [16]. Moreover, few HIIT interventions in children or adolescents have studied the effects on hepatic adiposity parameters, so further research is required.

Recently, Medrano et al. [18] proposed that a multidisciplinary intervention program including education healthy lifestyles, psychoeducation, and supervised exercise could play a key role in reducing hepatic fat and cardiometabolic risk in overweight children. In this context, four previous studies in children and adolescents examined the effect of supervised exercise without caloric restriction on hepatic fat [19–22]. However, the majority of the studies do not aim to identify non-traditional biomarkers as the surrogate end point of NAFLD. Previous reports observed changes in some circulating traditional biomarkers after liraglutide therapy [23] or exercise in NAFLD adults [24]. In obese youth, several P-selectins, endocan [25], insulin-like growth factor 1 [26], and some proinflammatory cytokines [27] have been proposed as biomarkers of endothelial dysfunction, dyslipidemia, inflammation, insulin resistance, and NAFLD. As far as we are aware, there are no previous studies identifying the profile of non-traditional biomarkers in adolescents at a high risk of NAFLD and the response to an intervention with exercise.

Given that physical exercise increases insulin sensitivity, increases oxidative metabolic activity, and reduces hepatic fat and cardiometabolic risk in a young obese population, the HEPAFIT study aims to examine whether a 6-month exercise program has benefits for hepatic fat content and inflammation as well as cardiovascular health outcomes among adolescents from Bogotá, Colombia, who are overweight or obese.

## Methods/design

### Study design, setting, and participants

The HEPAFIT study is a single-blind parallel-group randomized controlled trial (ClinicalTrials.gov ID NCT02753231). All parents or guardians will provide informed written consent and all the adolescents must give assent before being enrolled in the study. The study received ethical approval from the Medical Research Ethics Committee of the University of Rosario (ID UR-21042016). Random allocation to treatments will be performed at the individual level.

The study will include 100 adolescents (50% females) between 11 and 17 years of age attending to two public schools in the urban area of Bogotá D.C., Colombia. Inclusion criteria include primary overweight/obese status, defined according to the International Obesity Task Force [28], inactivity (no habitual participation in exercise more than once a week in the previous 6 months), and having at least one parent or caregiver willing to participate in the program sessions. Adolescents eligible for the present study will be invited to a pre-test, which will include a medical interview at the Centre for Studies of Physical Activity Measurements (in Spanish, CEMA), School of Medicine and Health Sciences, University of Rosario, Bogotá, Colombia. Risks will be minimized by identifying contraindications to the testing and training protocols via a health history and a thorough physical examination prior to the testing sessions. The exclusion criteria include having a clinical diagnosis of cardiovascular disease, having type 1 or type 2 diabetes mellitus, being pregnant, using alcohol or drugs, and not having lived in Bogotá for at least one school year. Adolescents with other causes of liver disease in the pediatric population that produce elevated liver enzyme levels will be excluded. These will be identified by screening for hepatotropic viruses (hepatitis A, B, and C, cytomegalovirus, and Epstein–Barr virus) and alpha-1 antitrypsin (A1AT) levels as well as autoantibodies and immunoglobulin G to rule out A1AT deficiency and autoimmune hepatitis, respectively. This study aims to investigate the effects of these interventions on risk factors for type 2 diabetes (i.e., its focus is prevention) rather than looking at their effects on treatment outcomes. Therefore, participants with established type 2 diabetes are excluded.

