### Recruitment

Consecutive boys or girls with overweight/obesity will be recruited from two public schools if they have received referrals from physician to either a primary- or secondary-care general practitioner in the capital district of Bogotá, Cundinamarca Department, in the Andean region. After completion of the informed consent process, adolescents who are interested in participating will be approached with further information and undergo pre-participation screening to determine contraindications to exercise using a cardiovascular and musculoskeletal checklist (including the patient’s medical history, disease history, and physical fitness). A member of the research team will follow up with a phone call to screen for eligibility and explain the main requirements of the study.

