### Blinding and randomization methods

The randomization into the four study arms will be performed by CEMA using a block randomization strategy with a block size of four. Since growing adolescents have an increasing body size and are undergoing developmental changes, a control group is necessary to detect changes due to training. After completing the baseline measurements, eligible participants will be randomly assigned to either the control or exercise training groups. The principal investigator will coordinate the allocation sequence, and randomization will be computer-generated. All participants and study personnel (including investigators, trainers, and statisticians) will be blinded to treatment allocation throughout the trial protocol. Access to the allocation code will be restricted to one study statistician who will not perform the final study analyses. Randomization will be conducted independently using sealed opaque envelopes. These procedures are also detailed in the study operations manual. Moreover, the importance of maintaining the blinding and allocation concealment will be reinforced by regularly scheduled conference calls at the sites and daily meetings with the field investigators (Fig. 1).

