The MOVI program uses attractive alternative materials not often used in the subjects’ daily lives or in the standard physical education classes. It is accessible, given that it occurs at the end of the classroom activities in the school’s facilities or nearby. It is free of charge and does not require the provision of any specific equipment. In its first edition, the MOVI program showed a moderate effect on reducing adiposity and improving the lipid profile but did not significantly improve global cardiometabolic risk or lower insulinemia [32]. In the second edition (MOVI-2), the duration and intensity of the sessions were increased and it was shown to enhance the development of muscle strength further. Likewise, analyses showed reduced adiposity in both sexes, and an improvement in the girls’ cardiovascular risk profile (low-density lipoprotein cholesterol or LDL-C and insulin) was observed [33]. The MOVI-2 program sessions that will be used in this work are the following:

Frequency: 3 days per week excluding holidays and vacation periods

Duration: 60 min, structured into 5 min of warm-up, 45 min dedicated to the main training curriculum, and 10 min dedicated to returning to a rest state

Protocol: Each of the sessions will work on activities based on health-related physical fitness (cardiovascular and muscle endurance and flexibility) at an intensity of between 8.0 and 11.7 metabolic equivalents (MET). All the games were performed previously by 32 schoolchildren during sessions of the MOVI-2 program while indirect calorimetry (through a portable gas analyzer), cardiac frequency, and accelerometry were evaluated for each game [34]. In addition, we have previously monitored the implementation of all the games with overweight/obese adolescents from Bogotá (unpublished observations).

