### Blinding and randomization

Each participant will have a 0.25 probability of being assigned to any study group. This assignment will be made through previously constructed balanced blocks. These blocks permit an equi-probabilistic assignment and ensure that each group has the same number of participants. This assignment mechanism will continue until all 100 participants have been assigned to their interventions. The study’s health personnel will act independently of the personnel in the school from where the participants are selected. Therefore, they do not carry out any school activities and their tasks are limited to collecting data for this study. The assignment codes will be maintained in a confidential file in the research center of the coordinating group and will be opened when the study analysis is finished. At the beginning and end of their participation in the study, the primary and secondary outcomes will be determined for each of the patients.

Given that physical exercise is an intervention that cannot be masked from the participants or researchers, professionals who are unaware of each subject’s group assignment will perform the measurement and analysis of the resulting variables. To ensure masking, randomization will be applied through balanced blocks and an alphabetical code will be assigned to each study group. This code will be in the custody of the administrative coordinator of the research group and will not be revealed to the professionals in charge of processing the data until the analysis with coded interventions has terminated.

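### The stated half-female sample is not secured by consecutive enrolment, and no stratification by sex is described, so visible chance sex imbalance between arms of 25 is likely (minor)

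*Protocol article*

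**What the plan says.** Under Study design, setting, and participants the sample is given flatly: "The study will include 100 adolescents (50% females) between 11 and 17 years of age". Under Recruitment the method is consecutive: "Consecutive boys or girls with overweight/obesity will be recruited from two public schools". No quota, cap or sex-specific target is mentioned there or elsewhere in the article.

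Allocation is described in two places. Blinding and randomization methods has CEMA "using a block randomization strategy with a block size of four". Blinding and randomization adds that "Each participant will have a 0.25 probability of being assigned to any study group", that the blocks "ensure that each group has the same number of participants", and that "This assignment mechanism will continue until all 100 participants have been assigned to their interventions". Neither place names a stratification factor. The only balance claimed is in the number per group.

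Sex appears elsewhere as a variable of interest:
- Background mentions sex differences among the reasons why the prevalence of paediatric NAFLD is uncertain.
- The section on the high-intensity class says that MOVI-2 reduced adiposity in both sexes and that "an improvement in the girls’ cardiovascular risk profile (low-density lipoprotein cholesterol or LDL-C and insulin) was observed".
- Sociodemographic information lists sex among baseline values that might act as covariates or confounders.

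Statistical analysis names no sex term for the primary or secondary models.

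**The concern.** A fixed half-female sample and consecutive enrolment to a fixed total are different designs. As written, staff cannot tell whether to stop taking one sex at 50 or to accept whatever split arrives. The only stopping rule given is the total of 100.

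If the lists do not use sex, arms of 25 will often differ visibly in their share of girls. Any outcome related to sex then carries extra noise in the between-arm comparison, and a reader of the baseline table will ask whether a difference reflects the programme or the mix of girls and boys. The question is most natural for lipids and insulin resistance. These are secondary outcomes here, and they are where the article itself reports an earlier benefit of the programme in girls.

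**Working it through.** **Inputs.** From the article: 100 participants, half of them girls, four arms of 25, equal allocation in blocks of four, and a target difference in hepatic fat of 5.0 with SD 4.1 (Power calculation and sample size). Assumed, because the article gives no figure: the true share of girls among those enrolled (40% to 50%) and the size of any sex effect on hepatic fat (1 to 4.1 points). The article does not derive the 50%, so there is no calculation to reproduce.

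**Step 1: overall split under consecutive enrolment with no cap.** The number of girls is taken as Binomial(100, p).

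| True share of girls p | P(exactly 50) | P(45 to 55) | P(outside 45 to 55) |
|---|---|---|---|
| 0.50 | 8.0% | 72.9% | 27% |
| 0.45 | 4.8% | 52.1% | 48% |
| 0.40 | 1.0% | 17.8% | 82% |

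Shares of 0.55 and 0.60 give the same results as 0.45 and 0.40. The 45 to 55 window is only a convenient yardstick.

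**Step 2: arm balance if the total is exactly 50 girls and 50 boys.** With lists that do not use sex, and sex unrelated to order of enrolment, the probability of k1, k2, k3, k4 girls in the four arms is C(25,k1)·C(25,k2)·C(25,k3)·C(25,k4) / C(100,50), with the k summing to 50. Summing over all splits (200,000 simulated allocations agree):
- SD of girls in one arm: √(25 × 0.5 × 0.5 × 75/99) = 2.18. The central 95% range is about 8 to 17 of 25.
- A given pair of arms differs by at least 5 girls (5/25 = 20 percentage points): 20.5%.
- Gap between the highest and lowest arm: mean 5.1 girls; at least 5 in 58%, at least 6 in about 41%, at least 8 in 15%.
- All four arms at 12 or 13 girls: 4%.

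**Step 3: what this does to the primary contrast.** The shift in a pairwise contrast is the difference in the share of girls multiplied by the sex effect. The expected shift is zero. At a 20-point imbalance it is 0.20 × 1 = 0.2 up to 0.20 × 4.1 = 0.8 points, against the target of 5.0. The SD of the difference in share between two arms is 0.142, so the chance shift has SD 0.142 × 1 = 0.14 to 0.142 × 4.1 = 0.58 points. The unadjusted standard error of a pairwise contrast is 4.1 × √(2/25) = 1.16.

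**Step 4: after stratifying by sex.** With 50 of each sex and blocks of four, each sex fills 12 complete blocks and leaves 2 over (4 × 12 + 2 = 50). Every arm therefore holds 12 or 13 girls and 12 or 13 boys, and arm totals run from 24 to 26. All four totals equal 25 only if the two incomplete blocks complement each other, which has probability 1/C(4,2) = 1/6, about 17%. The sample size is unchanged.

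**The case against.** The strongest reply has five parts.

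1. **Sex balance between arms is never promised.** The article claims equal numbers per group only. This stands: there is no contradiction on arm balance.
2. **Chance imbalance under valid randomisation is not bias.** Its expected effect is zero, and the test and interval allow for it. This also stands. A reader might infer from the imbalance figures that the comparison is confounded, but the documents do not support that reading.
3. **Silence on stratification is not a decision against it.** The article says "These procedures are also detailed in the study operations manual", and that manual is not shown. A reader might infer that randomisation ignores sex; all that can be said is that neither description names a stratifier.
4. **Protection already exists in part.** Sex is collected as a possible covariate, baseline comparability is monitored (Side effects and monitoring), and a multivariate analysis and control of baseline differences are planned (Statistical analysis). So it would be wrong to say that nothing protects the comparison. What remains is that none of these places commits sex to a model; the allowance for up to three predictors in the sample size section does not name them.
5. **The evidence on sex is indirect.** The benefit in girls concerns cardiovascular markers in an earlier study, where adiposity fell in both sexes. No section reports a sex-dependent effect of exercise on liver fat.

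Consecutive recruitment and a sex target could also coexist, if each sex were taken consecutively until full, or if the 50% were merely expected. That is possible, but the article does not say which is meant.

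**Conclusion.** Minor. The 50% split is stated as a fact, and nothing in the described recruitment or assignment ensures it. It may still occur, so it is not ensured rather than not delivered. With allocation as described, visible sex imbalance between arms of 25 is likely: about 20% for a gap of at least 5 girls in a given pair, and about 58% for that gap across the four arms. These figures assume exactly 50 girls in total, lists that do not use sex, and sex unrelated to enrolment order.

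The consequence is some loss of precision and interpretability, chiefly for secondary outcomes such as lipids and insulin. For the primary outcome it is small: 0.2 to 0.8 points at a 20-point imbalance, against a target of 5.0, on assumed sex effects of 1 to 4.1 points. The stronger readings, that the trial is biased or breaks a commitment to balanced arms, are not supported.

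**What to change.** 1. Use separate computer-generated block lists for girls and boys, and include sex as a factor in the primary and secondary models. At minimum, prespecify sex, which is already collected, as a covariate.
2. Reword the half-female statement as an expected composition. If a cap by sex is intended, say so under Recruitment.
3. Replace the claim of equal group sizes with approximately equal sizes.

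The cost is a second series of envelopes, one model term, and arm totals that may run from 24 to 26 instead of exactly 25, because 50 is not a multiple of four. A cap, if chosen, could slow the last enrolments; stratifying without a cap avoids that. The sample size does not change. If enrolment has already begun, the covariate and the rewording can still be adopted before the allocation code is opened.
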